# DISCOVER trial– Distal resection of the pancreas with or without coverage of the pancreatic remnant: study protocol of a randomised controlled trial

**DOI:** 10.1186/1745-6215-14-430

**Published:** 2013-12-14

**Keywords:** Coverage procedure, Distal pancreatectomy, Falciform ligament, Pancreatic fistula

## Abstract

**Background:**

Distal pancreatectomy for benign and malignant tumours is the second most common surgical procedure on the pancreas. Postoperative pancreatic fistulas (POPF) represent the most significant clinical complication, causing prolongation of hospital stay and the need for additional diagnostic and therapeutic procedures. Although various techniques for preventing POPF have been evaluated, to date, there is no available technique that ensures closure of the pancreatic remnant.

**Methods/Design:**

DISCOVER will aim to investigate differences in the postoperative course after a distal pancreatectomy comparing the standard surgical technique with an alternative technique that provides additional coverage of the pancreatic remnant by the falciform ligament. The primary endpoint of this trial will be the rate of POPF. As secondary endpoints, incidence of postoperative morbidity and mortality, length of hospital stay, and quality of life will be assessed.

DISCOVER is a single-centre, randomised, controlled surgical trial. For statistical analysis, a binary logistic regression model will be used. With a level of significance of 5% and a power of 80%, a sample size of 75 patients per group has been identified as necessary.

**Discussion:**

The findings of this trial will help to evaluate the usefulness of the coverage procedure at reducing the rate of POPF. The results could influence the standard procedure for remnant closure after distal pancreatectomy.

**Trial-registration:**

Clinical trials register (DRKS-ID: DRKS00000546)

## Background

A distal pancreatectomy is generally performed in cases of benign and malignant tumours of the pancreatic body or tail. Today, even advanced tumours with infiltration into neighbouring organs can be resected with good long-term outcome. Increasing numbers of diagnosed cystic lesions of the pancreas are a further reason for the increased need for distal pancreatectomies [1,2]. Despite low mortality rates in high-volume centres, the morbidity of this operation remains high, at up to 64% [3].

The most common morbidity following a distal pancreatectomy is postoperative pancreatic fistula (POPF). Insufficient healing of the resection margin causes leaking of aggressive pancreatic fluid into the abdominal cavity. Passive drainage tubes are routinely placed intra-abdominally in distal pancreatectomies. If any fluid from the abdominal cavity shows elevated levels of amylase on or after the third postoperative day, a POPF has to be assumed according to the consensus definition [4]. Most patients with a POPF are not limited by their physical condition and require no additional diagnostic or therapeutic steps; this condition is defined as a Grade A POPF. In these patients, the drainage tubes are removed slowly and in a stepwise manner during the following days or weeks, most often as an outpatient treatment. If they are not drained, these enzyme-rich intra-abdominal fluid collections often induce pain, lack of appetite, and vomiting, resulting in a prolonged hospital stay. Secondary bacterial infection of these collections can cause additional septic complications to varying degrees. Clinically impaired patients often need further therapeutic interventions such as nasogastric tubes, parenteral nutrition, antibiotics, and interventional drainage. Very rarely, angiography or further surgery is needed. Depending on the patient’s condition and the therapeutic interventions needed, the patient may be diagnosed with clinically relevant Grade B or Grade C POPF (Table 1).

**Table 1 T1:** **Definition and clinical grading of** POPF **according to the international study group on pancreatic fistula**

**Definition**	**Volume of drainage fluid on or after.**
**Grade A**	Clinical condition is good; at most little changes in management are needed. Hospital stay is not delayed; condition is managed by slow removal of drains.
**Grade B**	Clinical condition is often good; peripancreatic collection may occur. Specific forms of therapy, such as parenteral nutrition and antibiotics in cases of infection, are often needed. Endoscopic stenting of the main pancreatic duct may be necessary for sufficient drainage. Usually, hospital stay is delayed or readmission is required.
**Grade C**	Clinical condition is poor and stability may be borderline. Major changes in clinical management as intensive care and invasive procedures such as CT-guided drainage, angiography, or re-operations may be needed.

To date, various techniques for closure of the pancreatic stump have been tried and evaluated, including hand-sewn suturing, stapler closure, pancreatic duct ligation, ultrasonic dissection, pancreatoenteric anastomoses, application of meshes, and sealing with fibrin glue [3], yet none of these techniques can ensure a secure closure. New techniques are needed to avoid this complication.

### Preliminary data

Ever since distal pancreatectomies were first performed, there has been a longstanding debate as to the most effective technique for closure of the pancreatic remnant. For a long time, several different techniques were practiced side-by-side without good evidence in favour of or against any of them [5,6]. In 2005, a systematic review and meta-analysis verified this lack of evidence. Due to compromised comparability because of non-standardised surgical procedures or varying definitions of a POPF, the rates ranged from 0% up to 60% [7]. The DISPACT trial compared the two most commonly used techniques (hand-sewn suturing vs. stapler closure) in a large randomised multicentre trial. In that trial, the detected POPF rate was 36%, demonstrating that secure primary closure of the pancreatic resection margin is far from assured with the current techniques [3].

Recent reports have highlighted the potential advantage of additional coverage of the pancreatic remnant with autologous serous peritoneal tissue [5,6,8-13]. A prospective series from our institution confirmed that reduced rates of POPF were associated with shorter hospital stays and reduced treatment costs [14]. Closure with autologous patches is not a new technique, but it has long been underused. In the 1970s, peritoneal and pleural patches were used to prevent leakages in anastomoses after oesophageal and colorectal resections [15,16]. The falciform patch was initially used in the closure of duodenal and gastric perforations in high-risk patients [16]. In 2006, its use in the context of distal pancreatectomies was first described when skeletonised vessels were wrapped with a falciform patch to protect them from erosion bleeding due to POPF [17]. Iannitti et al. introduced the use of the falciform patch to cover pancreatic anastomoses in order to prevent POPF in pancreaticoduodenectomies and distal pancreatectomies in a retrospective series [10]. However, the results of recent studies highlighting this technique in distal pancreatectomies have to be interpreted with caution due to certain methodological drawbacks including mixed populations, inadequate or missing control groups, and non-uniform definitions of POPF.

## Study design

### Objectives and hypotheses

DISCOVER will aim to compare the effectiveness of additional reinforcement of the pancreatic stump by means of a coverage technique for preventing a POPF compared to hand-sewn closure alone in distal pancreatectomies.

The following hypotheses will be tested:

H_0_: The risk of developing POPF is equal in both groups.

H_1_: The risk of developing POPF is different between the two groups.

### Study population and location

The study population for the DISCOVER trial will consist of patients undergoing primary elective open surgery for benign and malignant tumours, chronic pancreatitis, or pseudocysts of the pancreatic body or tail. Detailed eligibility criteria are listed in Table 2.

**Table 2 T2:** Eligibility criteria

**Inclusion criteria**	**Exclusion criteria**
● Aged 18 years and over	● Current immunosuppressive therapy
● Disease of the pancreatic body or tail or involving this part of the gland and planned treatment consisting of elective open distal pancreatectomy	● Participation in another trial that might conflict with the endpoints of this trial
	● Pre- or intraoperative sign for obstruction of the pancreatic duct in the head of the gland
● Informed consent provided	● Lack of informed consent or compliance
	● Inability to follow the study-explanations
● Intraoperative: performance of a distal pancreatectomy	

This single-centre trial will be performed at a high-volume institution with experience in pancreatic surgery (Department of General, Visceral and Transplantation Surgery, University Hospital of Heidelberg, Germany). The clinical study centre of the surgical department (http://www.klinikum.uni-heidelberg.de/Willkommen.130058.0.html) will conduct the DISCOVER trial.

### Sample size calculation

The sample size calculation is based on the expected rate of POPF after distal pancreatectomy with and without additional coverage of the pancreatic remnant. The expected POPF rate of 16% in the experimental group is based on the results of all available studies [5,6,8-10] in which coverage of the remnant was performed and the internationally accepted definition of POPF was used (according to ISGPF [4]; Table 1). The POPF rate in the control group is expected to be 36% based on the 30-day follow-up results of the DISPACT trial in which no group received additional coverage. With alpha = 5% and beta = 20%, a sample size of n = 75 per group is necessary to detect a difference between the two groups when the χ^2^ test (two-sided analysis) is used. It can be expected that including covariates of prognostic importance (age, BMI, and extent of resection) in the logistic regression model that is applied in confirmatory analysis will increase the power as compared to that of the χ^2^ test.

### Ethics, study registration and consent

Before the start of recruitment, this trial was approved by the independent ethics committee of the University of Heidelberg and registered at the German Clinical Trials Register (DRKS-ID: DRKS00000546). The DISCOVER trial will be conducted in the context of Good Clinical Practice and in accordance with the Declaration of Helsinki.

All patients assigned for distal pancreatectomy at the Department of General, Visceral and Transplantation Surgery, University of Heidelberg, will be screened for eligibility on the day before the operation. During this preoperative visit, patients will be informed about the clinical problem of POPF, the timeline of the DISCOVER trial and the possible risks and benefits of participation before they will be asked to give their written informed consent.

### Randomisation and the intention-to-treat principle

Patients will be randomised intraoperatively once the surgical decision to perform a distal pancreatectomy has been made. Block randomisation was chosen and a random list was generated using the PROC PLAN feature of SAS software™ (Cary, NC, USA). The randomisation process will be paper-based (using sequentially numbered opaque envelopes) and performed by members of the study centre at our surgical department. If a distal pancreatectomy will be performed but the randomised procedure is not fulfilled, the patient will stay in the allocated group for analysis, according to the intention-to-treat principle. If the surgical procedure of a distal pancreatectomy is not accomplished, e.g., because of inoperability or the need for total pancreatectomy, the patient will be excluded from final analysis.

### Study treatment

#### Standardised surgical approach (control group)

The type of abdominal incision (longitudinal or transverse laparotomy) will be determined by the surgeon performing the procedure. After exploration of the abdominal cavity, the pancreas will be revealed and transsected by scalpel (fish-mouth technique) or by stapler. The pancreatic duct will be identified and closed by crossing stitches. The dorsal and ventral edges of the resection margin will be adapted using single stitches. Further manipulation of the pancreatic remnant such as use of fibrin glue or reinforcement with meshes will not be allowed.

The decision to perform an additional splenectomy or cholecystectomy is up to the surgeon’s preference. Further abdominal organ resections (e.g., multivisceral resection), as well as resection of vessels, do not conflict with the protocol.

Photodocumentation of the pancreatic stump should be performed before closure of the abdomen to document the type of stump closure. Furthermore, members of the clinical study centre will make unannounced visits during operations to observe the surgical closure technique used on the pancreas.

Just before abdominal wall closure, two passive drainage tubes will be placed at the pancreatic remnant for percutaneous drainage.

#### Experimental group

In patients randomly assigned to receive the coverage procedure, the falciform ligament will be separated from the abdominal wall and pulled through the minor omentum to the resection margin of the pancreas and will be fixed to the ventral and dorsal surfaces of the gland by single stitches or running suture, to cover the complete closed margin (Figure 1).

**Figure 1 F1:**
[figure not shown]
**Coverage procedure following distal pancreatectomy. ****(A)** The falciform ligament (fl) is separated from the abdominal wall **(B)** and pulled through the minor omentum. **(C + D)** Subsequently, a dorsal and ventral suture line (4–0 or 5–0 PDS) is used to fix the serosal surface of the ligament to the closed pancreatic stump (ps). vms = vena mesenterica superior; ahc = arteria hepatica communis.

If the falciform ligament cannot be used because of previous operations or for technical reasons, the gastric or jejunal wall can be used without opening of the intestinal lumen for the coverage procedure.

### Safety aspects of the coverage procedure

The falciform ligament and the ligamentum teres hepatis contained within it, which have no functional purpose in adults, are sutured to the pancreatic remnant by single stitches or running suture. A potentially elevated risk of developing delayed gastric emptying in patients with the falciform patch, as described in two reports cannot be excluded [5,8], but no additional complications associated with this interventional procedure have been described in the literature. Following the existing literature, it is expected that the coverage procedure will not extend operation time or increase blood loss, although both of these potential outcomes will be assessed as secondary endpoints within the trial [8,14].

### Adverse events and serious adverse events: accessing and reporting

An adverse event (AE) is any sign or symptom that impairs the patient’s well-being. A serious adverse event (SAE) is any AE that is life-threatening, prolongs hospital stay, results in persisting disability, or leads to death during the period of observation. AEs and SAEs will be recorded by means of daily postoperative ward visits until discharge and a telephone interview on postoperative day 40, performed by members of the study team (see below). All AEs of clinical relevance and all SAEs will be documented in the case report form. The trial investigator must be informed within 24 hours about SAEs that occur during hospital stay. The presence of a causal relationship between AEs or SAEs and the trial intervention will be judged by the investigator.

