### Postoperative data collection

Daily visits with study patients on all wards will be performed by clinical investigators and study nurses attached to the clinical study centre in order to collect information on the primary and secondary outcome parameters and to identify any AEs or SAEs. All surgeons will have to describe the closure technique that they performed on the pancreas on a standardised form that will be sent to them by email on the day of the index operation to record whether patients were treated according to the study protocol and were assigned to their groups truly at random. After discharge, all medical documents will be reviewed for assessment of the endpoints.

The DISPACT trial demonstrated an increased rate of POPF (30% to 36%) between day 7 and day 30 because this is when re-admission due to the need for further treatment occurred. To ensure the accurate assessment of our endpoints, DISCOVER patients will be called by phone at least 40 days after the operation to record postoperative development.

All patients will be invited to be seen at the outpatient clinic (European Pancreas Centre, Department of General, Visceral and Transplantation Surgery, Heidelberg) three months after their operation for regular follow-up consisting of oral and physical examination and blood tests. CT or MR imaging will be performed for regular follow-up, independent from this trial. The results will be used for postoperative data collection. Our flowchart summarises the data collection process with regard to timing and data type (Table 3).

**Table 3 T3:** Flowchart of the DISCOVER trial –course of examinations

**Visit**	**1**	**2**	**3**	**4**	**5**	**6**
	**Screening visit**	**Day of index OP**	**Daily postoperative ward visits**	**Day of discharge**	**Day 40 post OP (by phone)**	**3 months post-OP (optional)**
Past and current medical history	X					
Informed consent	X					
Physical examination and personal data (e.g., height, weight, age)	X					
Intraoperative randomisation (additional coverage yes/no)		X				
Basic study-related examination (to access endpoints)		X	X	X	X	X
Quality of life (EQ-5D questionnaire)	X			X	X	
AE, SAE		X	X	X	X	X
Drainage parameters (enzyme levels)			X	X		
Survival		X	X	X	X	X

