#### Confirmatory analysis

The null hypothesis of the proposed trial assumes that the rate of POPF type A–C is equal in the two intervention groups. A binary logistic regression model will be applied in order to compare POPF-rates in the two groups, adjusting for age, BMI and extent of resection. Confirmatory analysis will be based primarily on the full analysis set, which is consistent with the intention-to-treat principle as it includes all patients as randomised. Missing values will be replaced by means of the ICA-r method described by Higgins et al. [18]. Additionally, sensitivity analyses will be performed according to alternative methods for dealing with missing data, such as complete case analysis. In the final analysis, c_alpha = 0.0087 (alpha = 0.05, two-sided) will be applied.

Concerning the secondary endpoints, exploratory data analysis will be performed calculating appropriate summary measures for the empirical distribution (mean, standard deviation, median, minimum and maximum for continuous variables, and frequencies and percentages for categorical variables) as well as descriptive two-sided *P* values. Sensitivity analyses will be conducted for the perprotocol population as well as for the appropriate subgroup (e.g., covering methods). The safety analysis will include calculation and comparison of frequencies and rates of complications and SAEs. Furthermore, statistical methods will be used to assess the quality of the data and the homogeneity of the intervention groups. All analyses will be performed using SAS version 9.1 or higher.

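### The SAE definition counts a prolonged hospital stay but not a re-admission, so the SAE comparison between arms depends partly on when patients are discharged

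*Protocol article*

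**What the plan says.** The section on adverse events and serious adverse events gives this rule: "A serious adverse event (SAE) is any AE that is life-threatening, prolongs hospital stay, results in persisting disability, or leads to death" within the period of observation. The four criteria are joined by a single "or", with no catch-all item. The same section extends data capture beyond discharge: "AEs and SAEs will be recorded by means of daily postoperative ward visits until discharge and a telephone interview on postoperative day 40". The prompt-notice rule is narrower: "The trial investigator must be informed within 24 hours about SAEs that occur during hospital stay".

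Table 1 (Background) says of a Grade B fistula: "Usually, hospital stay is delayed or readmission is required". The section on postoperative data collection reports that the fistula rate in DISPACT, the earlier multicentre trial of stump closure, rose from 30% to 36% between day 7 and day 30, "because this is when re-admission due to the need for further treatment occurred". It gives this as the reason for the day-40 call.

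Under Confirmatory analysis: "The safety analysis will include calculation and comparison of frequencies and rates of complications and SAEs".

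On a separate matter, the section on safety aspects of the coverage procedure discusses operation time and blood loss and adds: "although both of these potential outcomes will be assessed as secondary endpoints within the trial". The Secondary endpoints section and its Table 4 name operation time only.

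**The concern.** Seriousness should follow from the event, not from where the patient was when it appeared. Under this rule, a fistula needing further hospital treatment becomes an SAE through a longer stay, but not through a new admission after discharge. The gap lies where the protocol itself expects part of its complications to occur.

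At stake is the between-arm comparison of SAE rates. Length of stay is itself an outcome that may differ between arms. If it does, like events may be labelled differently in the two arms for reasons unrelated to their severity.

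The blood-loss mismatch is a smaller matter: one section commits to an outcome that the endpoint list does not carry.

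**Working it through.** **1. Can re-admission be read into prolonged stay?** Three places in the article are relevant.

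- SAE definition: prolonged stay is named; re-admission is not.
- Table 1, Grade B: delayed stay and re-admission appear as alternatives joined by "or".
- Secondary endpoints: duration of hospital stay and need for re-admission are separate endpoints, and Table 4 defines the latter on its own.

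The protocol uses the two terms for different things, so the SAE rule cannot be taken to cover re-admission silently.

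**2. Effect on the comparison.** Consider only events that need hospital care and are not life-threatening, disabling or fatal. In each arm let r be their rate and s the share that appear before discharge and prolong the stay. The rule counts r × s and leaves out r × (1 − s). The ratio of counted rates, experimental (E) to control (C), is

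(r_E / r_C) × (s_E / s_C).

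It equals the true ratio only if s is the same in both arms. The documents give no value of s for either arm.

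**3. What the documents' figures can and cannot show.** The inputs are expected fistula rates of 36% (control) and 16% (experimental) with 75 patients per group (Sample size calculation), and the earlier trial's rise from 30% to 36% (Postoperative data collection).

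- Rise: 36% − 30% = 6 percentage points; 6 / 36 = one sixth of the fistulas counted by day 30.
- Control: 0.36 × 75 = 27 expected fistulas; one sixth is 4.5.
- Experimental: 0.16 × 75 = 12 expected fistulas; one sixth is 2.

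Suppose, purely for illustration, that every fistula were a candidate SAE and that the late sixth were lost in each arm. The counts would fall from 27 to 22.5 and from 12 to 10. The ratio would be unchanged (12 / 27 = 10 / 22.5 = 0.44), while the difference would shrink from 15 to 12.5, to the disadvantage of coverage. With equal event rates and earlier discharge after coverage, the distortion would instead favour coverage. The direction therefore depends on assumptions that the documents do not settle.

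**4. Sample size.** The stated 75 per group reproduces. With the pooled-variance formula for two proportions (mean 0.26), two-sided 5% and 80% power:

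n = [1.960 × √(2 × 0.26 × 0.74) + 0.842 × √(0.36 × 0.64 + 0.16 × 0.84)]² / 0.20² ≈ 74.3, rounded up to 75; power at 75 is 80.4%.

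Nothing in it depends on the SAE definition.

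**5. Blood loss.** The safety section names two outcomes as secondary endpoints. The endpoint text and Table 4 carry one of them, and blood loss appears nowhere else in the article. Postpancreatectomy haemorrhage is listed, but it is a postoperative complication and does not stand in for loss during the operation.

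**The case against.** The strongest reply is that nothing is lost from view. Fistula is the primary endpoint. Re-admission to any hospital for complications, intra-abdominal collections and revisions are all secondary endpoints. Clinically relevant AEs go into the case report form, and the safety analysis compares complications as well as SAEs. A re-admitted fistula therefore enters several comparisons, and only its SAE label is in question. That stands, and it limits the point. It does not make the label consistent, and the SAE rate is one of the quantities to be compared.

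A second reply is that the article condenses a fuller protocol. That covers detailed reporting procedures, so the limit of the 24-hour notice to the hospital stay is left aside: it is reporting logistics and does not alter the comparison. It does not cover the definition, which the article states in full.

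Two stronger readings are tempting. A reader might infer that the omission favours coverage because covered patients go home sooner. The section on preliminary data links shorter stays to fewer fistulas, not to equal complications moved past discharge, so this is unsupported. A reader might also infer that 4 or 5 of 75 control patients would escape the SAE count. That figure is a net rise in fistulas in another trial. It is not a count of re-admissions, no section says that patients are home by day 7, and some late fistulas would meet another criterion. Re-admissions for other causes are not in it at all.

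On blood loss, Table 4 is a summary and also leaves out the durations of stay that the text lists, so its silence alone proves little. The running text omits blood loss too.

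**Conclusion.** The point holds as a defect of classification. A complication of given severity may or may not be an SAE according to discharge timing, and the planned SAE comparison inherits this. The conclusion rests on reading the definition as the complete rule, which its wording supports, and on the protocol's own separation of prolonged stay from re-admission. Neither the direction of any bias nor the number of patients affected can be given from the documents. The primary analysis and the sample size are untouched. The change is worth making because it is cheap and the needed data are already collected.

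The blood-loss mismatch is real but minor. A reader might infer that blood loss will not be assessed at all; the safety section says that it will be, so the fault is an inconsistent list. Secondary endpoints are analysed only in an exploratory way, so no confirmatory conclusion depends on it.

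**What to change.** Add hospital re-admission to the SAE criteria. Apply the amended definition to both arms from the first patient onward by re-coding the re-admissions already recorded as a secondary endpoint. The cost is a wording change and a pass through existing records, with a somewhat higher SAE count and more reports as a small downside. Recruitment was still open when the article appeared.

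Separately, bring the safety section and the endpoint list into line by adding intraoperative blood loss to the Secondary endpoints text and to Table 4, with a definition and unit (for example ml).

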#### Secondary endpoints

Secondary endpoints will be postoperative morbidity including wound infection, intra-abdominal collection, delayed gastric emptying [18], postpancreatectomy haemorrhage [19], abdominal rupture, operation time, operative or interventional revisions, in-hospital mortality, duration of intensive care and hospital stay, need for readmission, and quality of life before operation, before discharge and at least 40 days after index operation according to the EQ-5D questionnaire (http://www.euroqol.org) (Table 4). The questionnaire that will be administered 40 days after the operation will be paper-based and sent to patients by post.

**Table 4 T4:** Summary and definitions of secondary outcomes

**Outcome parameter**	**Definition**
**Wound infection**	Surgical site infection associated with laparotomy that develops during the hospital stay
**Intra-abdominal collection**	Fluid collections in the surgical site with or without signs of infection, usually shown in CT-scans
**Delayed gastric emptying (DGE)**	Inability to tolerate solid food with prolonged need for nasogastric tube for at least four days or nasogastric re-intubation after POD 3; grading of DGE depends on its impact on clinical course and management; three grades are used for differentiation [18]
**Postpancreatectomy haemorrhage (PPH)**	PPH is classified, according to time of onset (early vs. late), severity (mild vs. severe) and diagnostic and therapeutic consequences (observation, transfusion, interventional, operative), into three grades [19]
**Abdominal rupture**	Dehiscence of abdominal closure with need for relaparotomy during 40 days after index operation
**Operation time**	Time from skin incision to closure of wound (minutes)
**Operative or interventional revisions**	All actions for diagnostic or therapeutic reasons that are related to an abnormal postoperative course are documented for analyses.
**In-hospital mortality**	Death of any cause during hospital stay
**Need for readmission**	Readmission to any hospital due to postoperative complications
**Quality of life**	Quality of life, accessed by using the EQ-5D questionnaire (EuroQol Group Foundation)

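### The SAE definition counts a prolonged hospital stay but not a re-admission, so SAE rates in both arms are understated and depend partly on discharge timing

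*Protocol article*

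**What the plan says.** The section on adverse events and serious adverse events gives the definition: "A serious adverse event (SAE) is any AE that is life-threatening, prolongs hospital stay, results in persisting disability, or leads to death". The list has no opening such as 'for example' and points to no fuller list. No other section of the article adds a criterion.

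The same section sets the recording window: "AEs and SAEs will be recorded by means of daily postoperative ward visits until discharge and a telephone interview on postoperative day 40". Table 3 also marks AE and SAE recording at the optional three-month visit. Prompt notification is narrower: "The trial investigator must be informed within 24 hours about SAEs that occur during hospital stay".

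Other sections bear on re-admission:

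- Table 1 (Background), on the Grade B fistula: "Usually, hospital stay is delayed or readmission is required".
- Postoperative data collection, on the DISPACT trial's rise from 30% to 36% between day 7 and day 30: "because this is when re-admission due to the need for further treatment occurred". The day-40 call is introduced for this reason.
- Table 4 (Secondary endpoints), defining need for readmission: "Readmission to any hospital due to postoperative complications". The list of secondary endpoints names duration of hospital stay separately.
- Confirmatory analysis, on how SAEs are used: "The safety analysis will include calculation and comparison of frequencies and rates of complications and SAEs".

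**The concern.** The protocol expects some fistulas to show themselves after discharge and keeps the SAE window open for them. An obvious way for such an event to become serious is that the patient has to come back into hospital, and this is not a criterion. Two patients with the same fistula and the same treatment can therefore be classified differently, according to whether they had already gone home.

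The between-group SAE comparison is at stake. A rate that turns on the date of discharge measures discharge practice as well as safety, and it understates serious events after discharge.

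**Working it through.** **1. Apply the definition to one fistula in two settings.** Take a Grade B fistula that is treated, does not threaten life, leaves no lasting disability and is survived.

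- Patient A is still in hospital and the stay is lengthened. The hospital-stay criterion is met, so this is an SAE.
- Patient B has been discharged and is re-admitted. None of the four criteria is met, so this is not an SAE.

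Table 1 gives A and B the same grade. Only the SAE label differs, and the only cause is whether the patient was still in hospital.

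**2. Can the hospital-stay criterion be read to include a second stay?** Table 1 joins delayed stay and re-admission with 'or'. The secondary endpoints list duration of stay and need for readmission separately. The article uses them as two concepts, so its wording does not support the wider reading.

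**3. Is patient B inside the SAE window?** Yes. Recording continues to the day-40 call, and Table 3 extends it to the three-month visit where that takes place.

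**4. Scale, for illustration only.** Inputs: 75 per group, 36% control and 16% experimental (Sample size calculation); 30% at day 7 and 36% at day 30 (Postoperative data collection).

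The plan's own figure reproduces. The two-sided chi-squared formula without continuity correction is n = [z(0.975) × √(2p̄(1−p̄)) + z(0.80) × √(p₁(1−p₁) + p₂(1−p₂))]² / (p₁−p₂)². With p₁ = 0.36, p₂ = 0.16 and p̄ = 0.26:

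- [1.960 × √0.3848 + 0.842 × √0.3648]² / 0.20² ≈ 74.3, which rounds up to 75 per group; power at 75 is 80.4%.

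The point does not depend on this figure; 75 only supplies the denominator below.

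- Late share of fistulas: (36 − 30) / 36 = 6/36 ≈ 0.167, or one sixth.
- Control: 75 × 0.36 = 27 fistulas, of which 75 × 0.06 = 4.5 are late.
- Experimental, assuming the same share: 75 × 0.16 = 12 fistulas, of which 12 × 0.167 = 2 are late.
- Together: 4.5 + 2 = 6.5 late fistulas among 150 patients.

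These are late fistulas, not missed SAEs. Some of these patients may still have been in hospital after day 7, some would never be re-admitted, and some would meet another criterion. Among these late fistulas, the number losing SAE status could lie anywhere from 0 to 4.5 in control and from 0 to 2 in the experimental arm. Re-admissions for other complications would add to this, but the article gives no figure for them.

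**The case against.** The strongest reply is that little is lost. All clinically relevant AEs go into the case report form. Re-admission to any hospital is a secondary endpoint, the safety analysis compares complications as well as SAEs, and fistula of any grade is the primary endpoint whatever its SAE status. Records are reviewed after discharge. The article ties no stopping rule or hypothesis test to the SAE count. All of this stands, and it confines the point to SAE classification and the SAE comparison.

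A second reply is that the article is condensed, and the full protocol or case report form guidance may add a criterion. That is possible. But the article states a complete definition, and a stated definition can be judged as it stands.

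A reader might go further and infer that the coverage arm will look safer than it is, because earlier discharge would turn prolonged stays into re-admissions there. The article does not support this. Its preliminary data link shorter stays to fewer fistulas; they do not say that covered patients who develop a fistula are sent home sooner. The illustrative figures above, if anything, take more events out of the control arm (4.5 against 2), which would narrow a difference in favour of coverage. That is not established either, since the common one-sixth share is an assumption.

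A reader might also take 4.5 and 2 as counts of SAEs that will be missed. They are not, for the reasons given with the calculation.

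**Conclusion.** The point holds as a fault in a stated rule. A re-admission that meets none of the four criteria is not an SAE, although the article elsewhere treats re-admission as the counterpart of a longer stay and keeps such events inside the SAE window. SAE rates in both arms are understated, relative to a definition that treats the two alike, and depend partly on discharge timing. The size and direction of any between-arm difference cannot be determined from the document.

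The late share of one sixth shows only that the group of events concerned need not be trivial. It rests on carrying the DISPACT pattern over to this trial and, for the experimental arm, on assuming the same share. The primary endpoint, sample size and confirmatory analysis are not affected.

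**What to change.** Add one criterion to the SAE definition: *requires admission or re-admission to hospital*. Apply it to both arms and to the whole observation period. State in the same place how the notification sentence, now limited to SAEs during the hospital stay, applies to events after discharge.

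Re-classify re-admissions already on file under the amended definition before the between-group safety comparison. The article says recruitment is still under way, so this can be done in time.

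The cost is one clause in the protocol, matching case report form guidance and the re-classification work. Re-admission is already collected as a secondary endpoint, so the new criterion should need no new data item. The downside is that reported SAE rates will be somewhat higher.
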